## Recording adverse events

Adverse events will be recorded by the investigator at each visit post-baseline. AEs will be documented in the medical notes in the first instance, and CRF following consent. When recording an adverse event, clinical symptoms and a simple, brief description of the event, including dates as appropriate, should be reported. Clinically significant abnormalities in the results of objective tests (e.g. laboratory variables) will also be recorded as AEs in the medical notes and if are assessed as serious they will also be recorded on the AE log and in the eCRF. If these events are not expected as part of disease or IMP, these will be recorded as unexpected. All adverse events will be recorded until 4 weeks after the end of treatment. At the end-of-trial assessment (i.e. four weeks after participant's end-of-treatment visit) a trial investigator will call the participants to collect any adverse event up until that point and this will be recorded in the medical notes and CRF following the same procedure as outlined above.

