### 519 Definitions

| Term                                                                              | Definition                                                                                                                                                                                                                                                                                                                                                                                                                                                                                                          |
|-----------------------------------------------------------------------------------|---------------------------------------------------------------------------------------------------------------------------------------------------------------------------------------------------------------------------------------------------------------------------------------------------------------------------------------------------------------------------------------------------------------------------------------------------------------------------------------------------------------------|
| Adverse Event (AE)                                                                | Any untoward medical occurrence in a patient or clinical trial participant administered a medicinal product and which does not necessarily have a causal relationship with this treatment. Therefore an AE can be any unfavourable or unintended change in the structure (signs), function (symptoms) or chemistry (laboratory data) in a participant to whom an IMP or procedural intervention has been administered, including occurrences which are not necessarily caused by or related to that product. |
| Adverse Reaction (AR)                                                             | Any untoward and unintended response in a participant to an investigational medicinal product which is related to any dose administered to that participant.

This includes medication errors, uses outside of protocol (including misuse and abuse of product)                                                                                                                                                                                                                                 |

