### Data collection tools and source document identification

Data will be collected using CRF. Source data will be accurately transcribed on to the CRF. Examples of source documents are medical records that included laboratory and other clinical reports. A source document list will be implemented prior to the start of the trial to identify data to be recorded firstly into source documents, such as medical notes and then transcribed onto the CRF.

The database and CRF will be designed in conjunction so that data captured are complete, accurate, reliable and consistent. The delegation log will identify all those personnel with responsibility for data handling including those who have access to the trial database.

The Investigators are responsible for ensuring the accuracy of all the data entered in the eCRFs. Source data and CRF data will be checked as being accurate, complete, reliable and consistent before it is entered onto the database by individuals delegated the responsibility outlined in the delegation log. This will include

- Screening data verification prior to randomisation to ensure patients fulfil the inclusion/exclusion criteria.
- Ensuring that all AEs are reported and recorded.
- Queries relating to eCRF entries are corrected within a suitable time frame.
- CRF will be checked for errors before being deemed as complete and this process will be documented.

A Data Manager will be appointed to ensure that appropriate corrections, additions, or deletions are made, dated, explained and initialled by the Investigator or by a member of the Investigator's trial staff who is authorised to initial CRF changes for the Investigator. A Data and Safety Monitoring Plan (DSMP) will outline trial procedures to be undertaken in ensuring data and safety monitoring throughout the lifespan of the Trial.

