| Outcome measures: | 
Primary outcome:
 
The primary objective of this trial is to compare the efficacy of 24-weeks of subcutaneous liraglutide 3.0 mg versus placebo administration, as an adjunct to diet and exercise, on %WL in participants with poor weight-loss and a sub-optimal active GLP-1 response following primary RYGB or SG at the end of the 24-week treatment period.
 
Secondary outcomes:
 
To compare the effect of 24-weeks of subcutaneous liraglutide 3.0 mg versus placebo administration as an adjunct to diet and exercise in participants with poor weight-loss and a sub-optimal active GLP-1 response following primary RYGB or SG, at the end of the 24-week treatment period, upon:
 

• Change in %WL over time (Week 2, 4, 8, 17 and 24)

• Change in fat, lean body mass and bone density.

• Change in circulating fasted glucose, insulin, HbA1c and leptin, and meal-stimulated glycaemic, gut hormone and appetite response.

• Change in HRQoL measures.

• Change in physical functional assessments.

• Safety as measured by the counts of adverse events.

 |
| Population:       | Subjects with poor weight loss response (<20% of their total weight) following 1 year or more primary gastric bypass or primary sleeve gastrectomy.                                                                                                                                                                                                                                                                                                                                                                                                                                                                                                                                                                                                                                                                                                                                                                                                                                                                                                                                                                                                                                                 |

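### The protocol gives conflicting instructions on whether non-serious but clinically significant test abnormalities enter the eCRF, so the SAP's adverse-event counts may omit them or include them inconsistently

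*Combined protocol and SAP*

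**What the plan says.** **Recording adverse events (protocol).** The general rule is that "AEs will be documented in the medical notes in the first instance, and CRF following consent". The section then deals separately with one class of event, abnormal results of objective tests such as laboratory variables. When clinically significant, these count as adverse events and are written in the notes. Entry anywhere else carries a condition: "if are assessed as serious they will also be recorded on the AE log and in the eCRF". The section closes by sending events collected at the end-of-trial telephone call to the notes and CRF by the same procedure.

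**Definitions (protocol).** An adverse event includes an unfavourable change in "function (symptoms) or chemistry (laboratory data) in a participant". No seriousness threshold is attached.

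**Data collection tools and source document identification (protocol).** "Data will be collected using CRF", with source data transcribed to it and checked before entry on the database. One of the listed checks is "Ensuring that all AEs are reported and recorded". The place of recording is not stated.

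**SAP.** The secondary outcomes in the Study Summary (section 1) include "Safety as measured by the counts of adverse events". The adverse-event paragraph in section 5.4 plans counts and nothing further. Section 3.3 describes analysis from the locked trial database. The SAP does not name the source of the adverse-event counts.

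**The concern.** One section tells the investigator both to put adverse events in the CRF and to put a particular kind of adverse event in the eCRF only when it is serious. Few laboratory abnormalities meet a formal seriousness criterion merely by being clinically significant, so the condition bears on the events that routine safety bloods exist to find: non-serious changes in liver, renal or thyroid function or in the blood count.

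At stake is the completeness and consistency of the safety outcome. If such events stay in the notes, they cannot appear in counts taken from the database. If one investigator applies the general rule and another the specific one, the counts depend partly on who did the recording.

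**Working it through.** No sample size, power or event-rate figure is involved, and the plan states no number to reproduce. The check sets the texts side by side.

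**1. Does the specific sentence restrict eCRF entry?** Under the general rule every adverse event, serious or not, reaches the CRF. Under the specific sentence a test abnormality reaches the eCRF if serious. If the general rule already covered non-serious abnormalities, the condition on eCRF entry would do nothing. The reading that gives it effect is that non-serious abnormalities stay in the notes. The protocol's Overdose section supports this: there the notes, eCRF and AE log are named as separate records, all to be updated, with no condition attached.

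**2. Does that conflict with other text?** Yes, in three places:
- the adverse-event definition, which covers laboratory changes without a threshold;
- the general rule in the same section;
- the data-check item requiring all adverse events to be recorded.

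In addition, the section on assessing adverse events asks for severity and causality for each event and ties the causality judgement to completion of the eCRF. An event kept out of the eCRF has no described place for that assessment.

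**3. Is there another route into the counts?** Data go from source to CRF to database, and the SAP analyses the database. No text describes moving events from the medical notes into the counts by any other path. That the counts come from the eCRF is therefore an inference from the only source described.

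**4. Would another planned summary show these events?** Fasted glucose and HbA1c are analysed as secondary outcomes, but as continuous measures, which adds nothing to adverse-event counts. The SAP plans no summary of liver, renal, thyroid or haematology safety results.

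**5. How much data is exposed?** The visit text lists haematology and biochemistry at screening, baseline and Visit 7. Visits 3 to 6 list none. Scheduled post-baseline safety bloods are therefore at most 70 participants × 1 visit = 70 sets. Laboratory variables are given only as an example of an objective test, so other or unscheduled tests could add to this. The documents give no expected rate of clinically significant abnormality, so the number of events cannot be derived.

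**6. What would it do to the comparison of arms?** Let the true counts of such events be A on liraglutide and B on placebo, with a recording fraction r common to both arms under blinding. The recorded counts are rA and rB. Their difference is r(A − B), and their ratio stays A/B as long as r > 0. If the specific sentence is followed throughout, r = 0 and this class vanishes from the counts. If practice is mixed, 0 < r < 1 and the difference shrinks. The documents give no value for A, B or r.

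**The case against.** The strongest reply is that this is an ambiguity and not an exclusion. The general rule, the closing sentence of the section, the requirement to assess each event and the all-events check all point towards CRF entry. The sponsor's SOP, which the protocol says governs recording of both serious and non-serious events, and the Data and Safety Monitoring Plan are not available here and may settle the practice. This stands. A reader might infer that every non-serious test abnormality is missing by rule; the documents do not support that, because they also contain the opposite instruction.

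It can also be argued that the specific sentence only adds an AE-log step for serious abnormalities, leaving the rest under the general CRF rule. This is weak: the sentence makes eCRF entry conditional as well as log entry. The documents do use CRF and eCRF without defining a difference, so the reading cannot be excluded altogether.

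A reader might further infer that the whole post-baseline laboratory safety assessment is lost. It is not. Serious abnormalities are captured, and the definitions extend seriousness to important medical events. Laboratory reports are among the source documents for the CRF, so the underlying values may be held even where no event is coded.

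Finally, safety counts appear in the SAP's Study Summary but not in the secondary outcomes of the protocol or of SAP section 4.2.2. The analysis is descriptive, and the same sentence applies to both arms under blinding. All of this limits the consequence. It does not remove the conflict.

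**Conclusion.** The recording instructions conflict and should be reconciled. If the specific sentence is followed, non-serious but clinically significant test abnormalities stay in the medical notes and are left out of the adverse-event counts; if practice varies, they are included inconsistently. This rests on one assumption, that the counts are drawn from the eCRF and database.

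The size cannot be stated as a number of events. Exposure is bounded at 70 scheduled sets of post-baseline safety bloods, plus any other objective tests that fall under the sentence. It would be tempting to say that the published safety table will look cleaner than the notes, or will favour one arm. The documents give no rate or arm difference from which to say either. The primary outcome is unaffected, and the events remain recoverable from the notes. This is a should-fix point.

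**What to change.** - **Protocol, Recording adverse events:** remove the seriousness condition, so that every clinically significant test abnormality judged to be an adverse event is entered in the AE log and eCRF with severity, causality and dates.
- **SAP, adverse-event paragraph in section 5.4:** state that the counts are taken from the eCRF.
- **Before database lock, while still blinded:** review the medical notes and enter any such events held only there. Staff without access to the randomisation code list should do this; the protocol says the trial coordinator and the trial pharmacist hold it. Entry after unmasking could be influenced by knowledge of allocation.

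The cost is one protocol sentence, one SAP sentence and modest data entry from existing notes for up to 70 participants.

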#### 431 End of Trial Assessment (Day 197) (+/- 3 days)

The investigator will call the participant 4 weeks after the last treatment injection to review and collect any adverse event that might have occurred since end of treatment. This final assessment will be carried out over the phone.

Participants who withdraw before the end of the trial will be asked to attend for their end-of-trial visit (as soon as possible after withdrawal) and their data will be imputed using last observation carry forward (LOCF) method. Withdrawn participants will not be replaced and no follow-up assessment will be carried out.

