#### Non adherence and adverse events

Descriptive statistics for characteristics of patients who do not adhere to their treatment as specified in the protocol will be presented. Adverse events will be summarised using counts.

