### 13. 5.5 Missing data/ Drop-out

Where possible, descriptive analysis of the characteristics of patients who withdraw consent will be performed and reasons for withdrawal will be described. A descriptive comparison of drop-out rates between trial arms will be undertaken using tabulations or graphs as appropriate. The characteristics of patients who drop out will be summarised where possible.

Bias due to missing data will be investigated by comparing the baseline characteristics of participants with and without missing values. Depending on the extent of missingness, the predictors of missing values will be identified using logistic regression. As part of a

1124 supportive analysis for the primary outcome, the predictors of missingness related to the  
1125 outcome will be included in the analysis model.

1126 Imputation of missing values of the primary outcome at week 24 may be performed using  
1127 the complete outcome values collected at other measurement time points if considered  
1128 appropriate or using self reported weight. Predictors of missingness and the predictors  
1129 included in the analysis model will be included in the imputation model. The missing values  
1130 will be imputed separately for each randomised group. The handling of missing data for the  
1131 analysis of the secondary outcomes will follow the same strategy if considered appropriate.

1132

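### The protocol's 4-week post-treatment adverse event window is not covered for withdrawn participants, and the SAP's safety counts name neither their unit nor the observation time

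*Combined protocol and SAP*

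**What the plan says.** **Collection.** The protocol's section on recording adverse events sets the window without exception: "All adverse events will be recorded until 4 weeks after the end of treatment". The End of Trial Assessment section (Day 197) gives the means: "The investigator will call the participant 4 weeks after the last treatment injection to review and collect any adverse event". The same section then turns to early leavers. They "will be asked to attend for their end-of-trial visit (as soon as possible after withdrawal"), and it adds: "Withdrawn participants will not be replaced and no follow-up assessment will be carried out".

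**Analysis.** The SAP's Study Summary lists among the secondary outcomes "Safety as measured by the counts of adverse events". The whole analysis text, in SAP 5.4 under non-adherence and adverse events, is "Adverse events will be summarised using counts". SAP 5.5 adds that "A descriptive comparison of drop-out rates between trial arms will be undertaken using tabulations or graphs as appropriate", but does not link this to the adverse event summary.

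**The concern.** Two things are at stake.

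The first is collection. A site cannot both record adverse events to 4 weeks after the last dose in every participant and make no further assessment of those who withdraw. If the end-of-trial section is followed as written, events in the weeks after an early stop are recorded only if they happen before the withdrawal visit.

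The second is the comparison. A completer is observed for 28 weeks, while someone who withdraws early is observed for less. A count with no denominator and no time base cannot show whether a difference between arms reflects the event rate, the time observed, or a few participants with repeated events. Knowing that drop-out differed by arm, which SAP 5.5 will show, warns the reader but does not supply the correction.

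**Working it through.** **1. The passages side by side**

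| | Participant who completes | Participant who withdraws |
|---|---|---|
| Window required (Recording adverse events) | to 4 weeks after end of treatment | the same; no exception stated |
| Contact planned (End of Trial Assessment) | phone call 4 weeks after last injection | one visit as soon as possible after withdrawal, then none |
| Window covered? | yes | no |

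The sentence ruling out follow-up stands under the heading for the Day 197 assessment, whose stated content is the adverse event call. It is therefore hard to read it as excluding efficacy visits only.

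**2. The plan's own figure, the source of the 20%**

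Inputs (protocol, Sample size calculation; SAP 4.2.1.1): difference 5 %WL, SD 5.4%, power 90%, significance level 5% (taken as two-sided), drop-out 20%.

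- Exact two-sample t-test: 25.5 per arm, rounded up to 26. Then 26 / 0.8 = 32.5, rounded up to 33 per arm, or 66 in total. This matches the stated figure.
- Normal approximation: 25 per arm. Then 25 / 0.8 = 31.25, rounded up to 32 per arm.

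The 20% is one overall allowance. It is not split by arm, time or reason.

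**3. Observation time**

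Inputs from the documents: 35 randomised per arm, and 28 weeks for a completer (24 on treatment plus 4). Planned total: 70 × 28 = 1960 person-weeks.

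Assumptions: 20% of 70 = 14 withdrawals, all at a common week w, with observation ending at about the withdrawal visit.

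Person-weeks in an arm with d withdrawals:

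- as written: (35 − d) × 28 + d × w
- with the 4-week call added: (35 − d) × 28 + d × (w + 4)

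Example, 10/4 split at week 4, as written:

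- arm with 10: 25 × 28 + 10 × 4 = 740
- arm with 4: 31 × 28 + 4 × 4 = 884
- ratio: 740 / 884 = 0.84

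| Split of 14 | Week | As written | Ratio | With call | Ratio |
|---|---|---|---|---|---|
| 7/7 | 2 | 798 / 798 | 1.00 | 826 / 826 | 1.00 |
| 7/7 | 17 | 903 / 903 | 1.00 | 931 / 931 | 1.00 |
| 10/4 | 2 | 720 / 876 | 0.82 | 760 / 892 | 0.85 |
| 10/4 | 4 | 740 / 884 | 0.84 | 780 / 900 | 0.87 |
| 10/4 | 17 | 870 / 936 | 0.93 | 910 / 952 | 0.96 |
| 14/0 | 2 | 616 / 980 | 0.63 | 672 / 980 | 0.69 |
| 14/0 | 4 | 644 / 980 | 0.66 | 700 / 980 | 0.71 |
| 14/0 | 17 | 826 / 980 | 0.84 | 882 / 980 | 0.90 |

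If the true event rate per week were constant and equal in both arms, expected event counts would stand in these ratios.

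**4. What each part of the remedy does**

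The call restores 14 × 4 = 56 person-weeks, or 56 / 1960 = 2.9% of the plan. It captures events after an early stop but hardly changes the ratio, because most of the lost time is the rest of the treatment period. Only a time base in the SAP deals with unequal observation.

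**The case against.** The other side has a good case on several points, and most of it limits the size of the concern.

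- **Withdrawn participants are contacted.** A reader might infer that they are dropped with no contact at all. The documents do not support that: a visit is requested soon after withdrawal, and events up to then can be collected. What is missing is the 4 weeks after the last dose.
- **Stopping the drug is not the same as leaving the trial.** The Dose modifications section stops treatment in participants who cannot tolerate 3.0 mg and does not mention withdrawal. The SAP's CONSORT template lists loss to follow-up and discontinued intervention separately. Someone who stops the drug but stays in the trial may still be within the window. The protocol does not draw this line clearly, so how many participants are affected cannot be settled from the text.
- **Counts may mean participants.** It is tempting to say that repeated events in one person will be counted many times. The SAP does not say so; the unit is simply undefined.
- **The direction of any bias is not fixed.** A reader might infer that the arm with more drop-out will look safer. That follows only if event rates are equal. If participants withdraw because of an adverse event, that event is already counted in their arm.
- **The weight is modest.** Safety appears in the SAP's Study Summary but not in the numbered secondary outcomes of SAP 4.2.2 or of the protocol. Secondary analyses are exploratory, and the drug is licensed. Severity, causality and seriousness are all to be assessed for each event.

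None of this removes the conflict between the two protocol sections or defines the counts.

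**Conclusion.** The concern holds in this limited form. The protocol requires a 4-week post-treatment window that its end-of-trial section does not deliver for participants who withdraw, and the SAP's safety summary has no stated unit and no observation time. Both follow from the text and need no assumption.

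Bias between arms is possible but not established. With 14 withdrawals, the person-week ratio runs from 1.00 (7/7 at a common time) through 0.82 to 0.93 (10/4) to 0.63 to 0.84 (14/0), for withdrawal at week 2 to week 17. The 14, the splits and the timing are assumptions. The 14/0 split is an extreme case, not a forecast. The rule on intolerance of the 3.0 mg dose makes a difference between arms plausible, but no more than that, and no single percentage should be quoted as the size of the bias.

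The primary %WL analysis is not affected. The point is worth acting on because safety is a listed outcome in the SAP summary and the remedy is cheap.

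**What to change.** **Protocol.** Reconcile the End of Trial Assessment section with Recording adverse events, so that the adverse event call 4 weeks after the last injection applies to every participant who took at least one dose, including those who withdraw, unless they decline contact. State which participants count as withdrawn, as distinct from those who have only stopped the drug.

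**SAP 5.4.** Replace the sentence on counts with a table giving, by arm:

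- the number and percentage of participants with at least one adverse event, overall and serious;
- the number of events;
- events per person-week, with observation time running from first dose to last adverse event contact.

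The rate should accompany the other two figures rather than replace them. It assumes a roughly constant event rate, and could mislead if events cluster early in treatment.

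**Cost.** At most about 14 phone calls at the planned drop-out (fewer if some decline contact or cannot be reached), one protocol clause and one extra table. If follow-up has already ended, the calls are no longer possible. The table still is, because it needs only dosing, contact and withdrawal dates, and SAP 3.1 allows adaptations that are justified openly.
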